## Abstract

**Background:**

Innovations in clinical training and support that enhance fidelity to evidence-based treatment (EBT) for adolescent behavior problems are sorely needed. This study will develop an online training system to address this gap: Measurement Training and Feedback System for Implementation (MTFS-I). Using procedures intended to be practical and sustainable, MTFS-I is designed to increase two aspects of therapist behavior that are fundamental to boosting EBT fidelity: therapist self-monitoring of EBT delivery, and therapist utilization of core techniques of EBTs in treatment sessions. This version of MTFS-I focuses on two empirically supported treatment approaches for adolescent conduct and substance use problems: family therapy and cognitive behavioral therapy (CBT).

**Methods/design:**

MTFS-I expands on conventional measurement feedback systems for client outcomes by adding training in observational coding to promote EBT self-monitoring and focusing on implementation of EBT treatment techniques. It has two primary components. (1) The *training component*, delivered weekly in two connected parts, involves self-monitored learning modules containing brief clinical descriptions of core EBT techniques and mock session coding exercises based on 5–8 min video segments that illustrate delivery of core techniques. (2) The *feedback component* summarizes aggregated therapist-reported data on EBT techniques used with their active caseloads. MTFS-I is hosted online and requires approximately 20 min per week to complete for each treatment approach. This randomized trial will first collect data on existing delivery of family therapy and CBT techniques for youth in outpatient behavioral health sites (Baseline phase). It will then randomize site clinicians to two study conditions (Implementation phase): Training Only versus Training + Feedback + Consultation. Therapists will choose whether to train in family therapy, CBT, or both. Study aims will compare clinician performance across study phase and between study conditions on MTFS-I uptake, reliability and accuracy in EBT self-monitoring, and utilization of EBT techniques in treatment sessions (based on observer coding of audiotapes).

**Discussion:**

Study contributions to implementation science and considerations of MTFS-I sustainability are discussed.

**Trial registration:**

ClinicalTrials.gov, NCT03722654. Registered on 29 October 2018.

## Background

### Family therapy and cognitive behavioral therapy are prime candidates for improving the quality of treatment for adolescent externalizing problems

Disseminating effective methods to improve the quality of available treatment services for adolescent externalizing problems (AEPs) in behavioral care is an urgent public health priority. There remains a troubling “quality gap” between behavioral treatments proven in controlled research versus those commonly practiced in usual care [1]. This gap is highly evident for AEPs, which encompass serious conduct problems, delinquency, and substance misuse. AEPs are the most common adolescent behavioral issues in specialty care, which follows from their high prevalence rates. In the USA, for example, conduct disorder has a 1-year population prevalence among youth ranging from 2 to 10% [2]; 15% of adolescents meet diagnostic criteria for alcohol use disorder and 16% for substance use disorder by age 18 [3]; and 31 million youth are involved in the juvenile justice system, with approximately 1.5 million new youth arrested each year [4]. Moreover, comorbidity between conduct and substance use problems is the rule rather than the exception among clinic-referred teenagers [5]. Yet standard treatment quality for AEPs is considered mediocre to inadequate due to a host of factors headlined by the absence or modest quality of evidence-based services, insufficient provider training, and little or lax quality monitoring [6, 7].

Two behavioral treatment approaches are prime candidates for upgrading the quality of AEP treatment services. Both family therapy (FT) and cognitive behavioral therapy (CBT) have excellent efficacy evidence for AEPs in both research and community settings [7, 8]. Each has strong support from research conducted in several countries for treating serious conduct problems [7–9], delinquency [7, 10], and substance use [6], and each has several manualized versions proven efficacious across the AEP range. Due to this extensive evidence base, there is incentive from clinical providers and payers to deliver these approaches in routine care: Both are now approved for treating AEPs by third-payer insurance plans and by regulatory agencies that govern licensed treatment providers (e.g.,). Notably, therapists report that both are highly valued in everyday practice [11, 12].

### Boosting fidelity to evidence-based treatment is a royal road to improving quality

An efficient pathway to improving the quality of behavioral health services is to increase the adoption and delivery of evidence-based treatments (EBTs) in usual care [1]. However, there is a caveat: For EBTs to be effective in front-line settings, they must be delivered with sufficient fidelity to the core principles and techniques of the approaches they represent. This remains a most difficult challenge for which innovative solutions are sorely needed [13]. With regard to AEPs, controlled studies have shown that strong fidelity to the FT and CBT approaches predicts improved client outcomes in both efficacy [14] and effectiveness [15] studies. Moreover, greater utilization of core EBT techniques for AEPs predicts better youth outcomes even when services are provided by community clinicians not trained in manualized treatments [16]. Yet at this time neither FT nor CBT is widely implemented with fidelity in community clinics that treat AEPs [1].

Given that stronger fidelity to EBTs can lead to improved outcomes for youth with AEPs, innovations in clinician training and support designed to increase fidelity to the FT and CBT approaches are sorely needed. The current study will develop a pragmatic online training system to achieve this goal. The study protocol is a randomized trial that will test a Measurement Training and Feedback System for Implementation (MTFS-I; see [17]) to increase fidelity to FT and CBT in behavioral care. MTFS-I is an example of a “learning” quality improvement system in which EBT delivery activities are carried out incrementally, implementation and sustainability data are regularly reviewed, and continuous EBT modifications are made to increase fit and/or feasibility ([18]). Learning systems are intended to ingrain data-driven decision-making into the procedural routines of agencies.

As next described, MTFS-I is designed to increase two aspects of therapist behavior that are fundamental to boosting EBT fidelity in a manner that is sustainable with typical agency resources [19]: therapist self-monitoring of EBT fidelity, and therapist utilization of EBT techniques in treatment sessions. MTFS-I traffics in EBT “core elements” [20] rather than full manualized protocols. EBT core elements are operationalized as discrete treatment techniques that are common ingredients of multiple EBT protocols for a given disorder. Core elements are considered easier to master than full EBT manuals, and they equip clinicians with a diverse portfolio of techniques that can be judiciously applied to clients presenting with comorbid, heterogeneous, and/or emerging clinical problems, making them well suited for the eclectic treatment practices that constitute usual care.

### EBT fidelity boost, part 1: train therapists to self-monitor by mimicking observational coding methods

One major step toward boosting the capacity of community therapists to implement EBTs with fidelity is improving their ability to accurately monitor (i.e., recognize and assess) the EBTs they are expected to deliver. There is consensus that training clinicians to self-report accurately on EBT delivery is a pragmatic strategy for tracking and ultimately improving EBT fidelity in usual care [19]. Self-report fidelity procedures are quick, inexpensive, non-intrusive, and compatible with electronic medical record systems, making them sustainable in everyday service contexts. They are also flexible in that they can capture fidelity to specific treatment manuals or to core treatment techniques associated with evidence-based approaches [21].

However, for fidelity self-monitoring to be useful, there remains a major psychometric hurdle to clear: Studies attempting to confirm the validity of therapist self-ratings of EBT fidelity by comparing them with observer ratings have mostly produced disappointing results, casting doubt on the accuracy with which therapists can judge their own performance. Research with both adult and youth populations has logged modest to weak concordance between therapist and observer reports of fidelity to various EBTs. And although a handful of studies (e.g., [21]) have found moderate *reliability* (i.e., adequate correlations) between therapists and observers when reporting on EBT utilization, these studies also found that therapists showed uniform *inaccuracy*: They reported much greater average use of EBTs (i.e., significantly higher mean fidelity scores) than did observers. Overall, weak concordance with trained observers is a universal therapist bias that affects research-trained clinicians delivering manualized EBTs as well as clinicians in usual care.

This study will develop an innovative strategy for improving therapist self-monitoring (reliability and accuracy) of EBT fidelity: teach clinicians to be fluent in self-rating by employing rigorous training procedures analogous to those used to train observational fidelity raters in controlled research. Unfortunately, gold-standard observational methods are resource-intensive, requiring numerous hours for introducing the coding scheme, reviewing recordings outside training sessions to calibrate scoring, and convening meetings throughout coding activities to prevent coder drift. Directly transporting these methods from research labs to everyday care—that is, training agency staff to reliably assess EBT use by supervisees or colleagues—is well beyond the resource capacity of most providers. However, some have asserted that by mimicking observational methods when training community therapists to self-monitor, it is possible to improve the reliability and accuracy of therapist-reported EBT fidelity [19]. Is this approach feasible? Front-line therapists can be trained to report EBT fidelity reliably under *ideal* conditions, that is, as research-trained judges in lab settings [14]. But can they be trained to self-monitor fidelity under the *pragmatic* conditions that prevail in usual care?

The self-monitored training method most likely to succeed is online instruction, a research-proven approach wherein training content can be presented in a user-tailored manner [22]. Brief online methods appear to be an excellent surrogate for gold-standard methods to increase therapist capacity to validly assess their own EBT fidelity. This study’s approach to mimicking observer training is as follows: Over the course of 1 year, clinicians will receive weekly email prompts to view online, brief (5–8 min) video vignettes, each demonstrating a selection of core FT and CBT treatment techniques they are hoping to deliver. After viewing each vignette, therapists submit fidelity rating scores for a selection of techniques (covering the full roster over time); they are then immediately shown gold-standard rating scores for the given vignette for direct comparison with their own ratings.

### EBT fidelity boost, part 2: adapt measurement feedback systems to strengthen EBT utilization

Another major step toward boosting EBT fidelity in usual care involves adapting measurement-based care (MBC) methods. MBC is a performance feedback loop in which a given quality metric is continuously monitored by a clinician to gauge case progress and support clinical decision-making [23]. To date MBC has been used in behavioral care primarily to monitor client outcomes, wherein the outcome metrics are standardized measures of client functioning. MBC feedback loops are often supported by the use of measurement feedback system (MFS) technology that generates easy-to-digest data reports providing summary appraisals of client progress compared to a desired benchmark. MBC has led to impressive gains in treatment outcomes across diverse adult clinical samples (e.g., [24, 25]). Also, clinicians trained in MBC can develop positive attitudes toward it [25]. MBC research with youth samples is new, but there is strong enthusiasm about reaping comparable benefits [25].

MBC success for client outcomes has generated enthusiasm for developing comparable procedures for routine feedback of treatment implementation data [23, 24]. When attuned to treatment delivery processes such as EBT fidelity, MBC can serve as a functional quality assurance procedure with broad dissemination potential for youth behavioral care [23]. This study’s approach to adapting MBC for implementation data involves summarizing therapist self-reports of FT and CBT technique delivery in user-friendly infographics distributed to clinicians and supervisors on a monthly basis. MFS technology has already been incorporated into quality procedures to bolster fidelity for several standardized protocols [23, 24], although the validity of therapist-reported EBT use for these protocol-based systems is not yet well established via concordance with observer ratings.

There is also reason to believe that adapted MBC methods providing feedback reports on EBT implementation can increase EBT use even if therapists are not ultimately accurate in EBT self-monitoring. Regular review of feedback reports by clinicians and supervisors can spur direct comparison between therapist self-reports of EBT fidelity versus agency-specified fidelity benchmarks, precipitating self-correction responses that should guide movement toward agency fidelity goals [24]. Also, case feedback along multiple dimensions, including routine feedback on treatment processes like EBT fidelity, is thought to optimize change potential [23]. And in addition to effects from EBT implementation feedback, EBT utilization can be increased by the online training procedures described above: Providing therapists with videos that model high-fidelity FT and CBT techniques creates a forum for observational learning of EBT delivery and prompts attention to EBT-infused service delivery.

### Protocol summary and specific aims

Family therapy and CBT have strong effectiveness evidence for AEPs but remain widely underutilized in clinical practice. This study tests a clinician training system, MTFS-I, designed to increase delivery of these EBTs in behavioral health services internationally. MTFS-I expands on conventional MFS technology by (1) adding *Training* in observational coding to promote EBT self-monitoring and (2) focusing on *Implementation* in the form of fidelity to core EBT techniques. Figure 1 depicts the basic training process by which MTFS-I is meant to produce effects on EBT self-monitoring and technique use, including the intervention components, targets, putative mechanisms, and impact of the training. The observational coder training and implementation feedback components contained in MTFS-I are functionally symbiotic: Training is meant to ensure that clinicians generate valid self-report data to anchor feedback reports, and feedback reports supply motivational context for dedicated participation in self-monitored training. The putative learning mechanisms—cognitive, behavioral, attitudinal [26]—activated by the two intervention components await confirmation and articulation via direct testing. It is critical to note that MTFS-I is not intended to be a “replacement approach” in which clinicians are trained to implement new EBTs, but rather an “augmentation approach” aimed at enhancing expertise for EBTs already endorsed and practiced to some degree [13].

**Fig. 1 Fig1:**
[figure not shown]
Training process schematic: Measurement Training and Feedback System for Implementation (MTFS-I) of FT and CBT techniques

This randomized trial will first collect data on existing delivery of FT and CBT techniques for youth with AEPs in four outpatient behavioral health sites (Baseline phase). It will then experimentally compare the boost in FT and CBT fidelity produced when clinicians are randomized to one of two study conditions (Implementation phase): Training Only versus Training + Feedback + Consultation. Study data will include (1) post-session therapist-reported checklists on EBT use and (2) audiotapes of treatment sessions that will be observationally coded by research staff. Study Aim 1 will compare Baseline versus Implementation phases in EBT self-monitoring and EBT utilization, combining across sites. We expect that both self-monitoring (reliability, accuracy) and technique use (FT, CBT) will be significantly greater during the Implementation phase, after initiation of MTFS-I training. Study Aim 2 will experimentally test the effects of one MTFS-I component (Training Only) versus a full MTFS-I package that includes both system components plus ongoing expert facilitation (Training + Feedback + Consultation). We expect that Training + Feedback + Consultation will be superior to Training Only in promoting EBT self-monitoring and technique use. We will also examine the strength of correlation between self-monitoring and technique use via within-subject (comparing study phases) and between-subject (comparing study conditions) analyses.

## Methods/design

### Trial design

The trial design is a two-group randomized trial with baseline comparison: Following a 4-month Baseline phase, therapists working in behavioral health treatment sites will be randomized across two experimental conditions, Training Only versus Training + Feedback + Consultation, for a 1-year Implementation phase. During both study phases we will collect EBT fidelity data (therapist-reported checklists, session audiotapes); during the Implementation phase we will also collect MTFS-I uptake data (training and consultation activity). In Aim 1, by comparing Baseline versus Implementation data, we can examine the effectiveness of the MTFS-I training component for enhancing EBT fidelity across study sites, yielding proof-of-concept data in accord with the well-established Stage Model of behavioral treatment development [27]. In Aim 2, by experimentally comparing Training Only versus Training + Feedback + Consultation, we can test the added value of MBC procedures combined with expert consultation procedures [26] for enhancing MTFS-I benefits. Also the quasi-experimental analysis of Baseline data (averaged across all study therapists) versus Training Only condition data will shed light on the unique effects of the online training component, which is the most pragmatic feature of the overall MTFS-I package. Comparing averaged Baseline-phase data versus the Training + Feedback + Consultation condition will also provide insight on the full MTFS-I effects. It was not possible to include a no-intervention or waitlist control group because sites unilaterally preferred that all study therapists receive a clinically meaningful training experience. To maximize clinical utility and trainee motivation, each study therapist will select whether they want to train in FT, CBT, or both; training in both approaches will double the time commitment (to approximately 40 total min per week) for the given trainee. Figure 2 is the Standard Protocol Items: Recommendations for Interventional Trials (SPIRIT) diagram depicting the schedule of trial enrollment, interventions, and assessments. Additional file 3 presents the SPIRIT checklist. Study sites and eligibility, sample size, randomization, and contamination procedures.

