**Fig. 2 Fig2:**
[figure not shown]
SPIRIT diagram depicting the schedule of trial enrollment, interventions, and assessments

To host trial activities we will recruit four behavioral health outpatient clinics that attest to endorsing FT and CBT as staples of their clinical practice. All full-time clinicians will be eligible to participate. We project to enroll 32 therapists total (8 therapists per site [6 active slots plus 2 to replace dropouts]) treating 192 cases (24 therapist slots × 8 consenting cases/year). Treatment will average ~ 6 sessions/case (given routine therapy attrition), yielding ~ 1152 post-session therapist-reported checklists, about half with accompanying recordings (*n* ~ 576); half of these (~ 288 sessions) will be coded for EBT fidelity by research staff. Figure 3 shows a Consolidated Standards of Reporting Trials (CONSORT) flow chart of projected study enrollment. We will randomize volunteer therapists within each site to study condition at the start of the Implementation phase, given that MTFS-I procedures target individual therapists and their supervisors rather than entire agencies [24]. We will not randomize supervisors to condition, for two reasons. Because therapists in the Training Only condition will engage in solitary online training activities and will not review feedback reports or participate in expert consultation meetings with supervisors, we do not anticipate substantial supervisor “crossover” effects should a given supervisor oversee therapists in both conditions. Also, many clinics have only one supervisor, making it neither practical nor ecologically valid to randomize supervisors into condition. To guard against experimental contamination, supervisors will be asked not to review feedback reports in the presence of Training Only therapists.

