### Data analysis plan

Study data will have a three-level nested structure: clients within therapists within sites (we will average across sessions for each client). The basic analytic approach for these nested data will be multilevel mixed effects models examining the effects of Phase (Baseline versus Implementation) and Condition (Training Only versus Training + Feedback + Consultation) on dependent variables aggregated across each time period: 4-month Baseline phase (prior to MTFS-I training) and 12-month Implementation phase. We will use maximum likelihood estimation for continuous variables and robust weighted least squares for categorical variables. We will model Site and Therapist as random effects in all models. We will include Therapist (age, sex, race/ethnicity, experience, EBT attitudes, EBT proficiency) and Client (age, sex, race/ethnicity) factors at their respective levels to examine potential effects. Effect sizes will be calculated using the standardized *d* effect size indicator, interpreted as the standardized difference between contrasts for Phase and Condition comparisons [41]. Aim 1 exploratory contrasts will examine the Phase (within-subjects) effect, contrasting Baseline versus Implementation across all sites in EBT self-monitoring (reliability, accuracy) and EBT technique use (averaging across FT and CBT techniques). Aim 2 will experimentally test the Condition (between-subjects) effect on MTFS-I uptake, EBT self-monitoring, and EBT technique use.

To analyze EBT self-monitoring, reliability between therapists and observers on FT and CBT technique use will be calculated using the ICC_2,2_ [44]. Conditions will be compared on the relative magnitude of ICCs for each EBT scale. To compare conditions on therapist accuracy, we will use statistical equivalence testing methods, applying the confidence interval approach [45] to examine whether therapist scores are equivalent to corresponding observer scores. To analyze EBT technique use, a series of multilevel mixed effects models will be conducted with a dummy-coded Condition variable included at the Therapist level to test the contrast of main interest; alpha will be adjusted to account for multiple contrasts. For the Aim 1 analyses of Phase contrasts, a product interaction terms will be included to examine Phase by Condition effects; for significant interactions, we will test simple effects by examining Phase contrasts separately within condition.

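### Aim 1 presents a Baseline-to-Implementation change pooled over both conditions as the effect of training; the unconditional Training Only contrast in the design section is not carried into the analysis plan

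*Protocol article*

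**What the plan says.** Therapists are randomized to "Training Only versus Training + Feedback + Consultation, for a 1-year Implementation phase". For Aim 1, Trial design says that with the Baseline versus Implementation comparison "we can examine the effectiveness of the MTFS-I training component for enhancing EBT fidelity across study sites". The Data analysis plan defines the comparison: "Aim 1 exploratory contrasts will examine the Phase (within-subjects) effect, contrasting Baseline versus Implementation across all sites". That contrast covers therapists in both conditions.

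Trial design then adds two further comparisons, neither tied to any prior test. For online training: "Also the quasi-experimental analysis of Baseline data (averaged across all study therapists) versus Training Only condition data will shed light on the unique effects" of that component. For the whole package: "Comparing averaged Baseline-phase data versus the Training + Feedback + Consultation condition will also provide insight on the full MTFS-I effects".

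The Data analysis plan lists neither. It adds a Phase by Condition product term to the Aim 1 models and says that "for significant interactions, we will test simple effects by examining Phase contrasts separately within condition".

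The section on protocol summary and specific aims states the expectation that Training + Feedback + Consultation will outperform Training Only on self-monitoring and technique use.

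**The concern.** Two things do not fit together.

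The first is the name given to the pooled contrast. Some therapists contributing Implementation data also receive feedback reports and expert consultation. The pooled change reflects training alone only if those additions do nothing, and the protocol's own hypothesis is that they do something.

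The second is the route to a training-only result. Trial design offers one without conditions, against a Baseline averaged over all therapists. The Data analysis plan offers within-condition Phase contrasts only when the interaction is significant, and there the natural comparator is that condition's own Baseline. If the interaction is not significant, an analyst following Trial design reports a Training Only result, while one following the Data analysis plan has no instruction to do so.

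At stake is how the online training is read. Trial design regards it as the most practical part of the package, so it is the result that agencies without money for consultation would look to.

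**Working it through.** **What the plan's power figure covers.** The Power analysis section gives power only for the between-condition effect (above .80 at d = .30). It gives none for the Phase contrast or the interaction, so there is no figure to reproduce on this point. For completeness: with 144 tapes per arm, a design effect of 1 + (9 − 1) × .05 = 1.40 and an assumed two-sided alpha of .05, power at d = .30 comes to .58. That is a separate matter, possibly explained by software inputs not reported, and nothing below depends on it.

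**Inputs from the protocol.** 288 coded tapes; 32 therapists; ICC .05; planning effect d = .30; d = .40 to .50 from previous research with a similar design (Power analysis); phases of 4 and 12 months (Data analysis plan).

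**Assumptions.** The text gives no allocation ratio, no split of tapes between phases and no numerical alpha. I take 1:1 allocation, a 1:3 split following the phase lengths (72 Baseline, 216 Implementation tapes) and two-sided .05, and vary the first two.

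**Step 1: what the pooled contrast estimates.** Let T be the Baseline-to-Implementation change under Training Only, b the increment from Feedback + Consultation, and p the full-package share of Implementation data.

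Pooled Phase contrast = (1 − p) × T + p × (T + b) = T + p × b.

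This equals T only if b = 0. The excess p × b is:

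| Share p | b = .30 | b = .40 | b = .50 |
|---|---|---|---|
| 1/3 | .10 | .13 | .17 |
| 1/2 (1:1) | .15 | .20 | .25 |
| 2/3 | .20 | .27 | .33 |

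Under 1:1 with T = 0 and b = .40, the pooled contrast is .20 although training alone changed nothing.

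**Step 2: how often the interaction would be significant.** Unit variance is assumed, with stable therapist effects that cancel between phases, leaving residual variance 1 − ICC. With two conditions of equal size:

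SE = sqrt[(1 − ICC) × (4/72 + 4/216)] = sqrt[(1 − ICC) × .0741], which is .272 at ICC 0 and .265 at ICC .05.

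Power ≈ Φ(b/SE − 1.96):

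- b = .30: .20 (ICC 0) and .20 (ICC .05)
- b = .40: Φ(1.470 − 1.96) = .31 and Φ(1.508 − 1.96) = .33
- b = .50: .45 and .47
- b = 0: .05 by construction

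An even split (144/144) gives .40 to .41 at b = .40. If the 288 tapes were all Implementation tapes, with 96 Baseline tapes added (384 in total, more than the protocol states), the result is the same .40 to .41.

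The calculation treats tapes as units, whereas the Data analysis plan averages sessions within client. Correlation between tapes of one client, therapist changes that vary between phases, or the planned alpha adjustment (if it covers the interaction) would lower these figures. Useful covariates would raise them.

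**Step 3: precision of the alternatives** (ICC 0, 72/216 tapes).

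- Pooled Phase contrast: sqrt(1/72 + 1/216) = .136
- Training Only against its own Baseline: sqrt(2/72 + 2/216) = .192
- Training Only against all-therapist Baseline: sqrt(1/72 + 2/216) = .152

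**The case against.** The strongest reply is that Trial design already separates training from the package. It plans "the quasi-experimental analysis of Baseline data (averaged across all study therapists) versus Training Only condition data" unconditionally, with a matching full-package comparison. The Data analysis plan does not withdraw these, and a condensed article need not list every contrast twice. The interaction rule governs follow-up tests, not whether an estimate exists. With a dummy-coded Condition and a product term, the Training Only change is one coefficient or a simple combination of coefficients. The claims are also hedged: proof of concept, quasi-experimental, exploratory. Aim 2, the randomized comparison, is untouched.

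Most of this stands, and it rules out two stronger readings. A reader might infer that the Training Only result will usually go unreported, or that online training could be declared effective with nothing in the plan to show otherwise. The documents do not support either, because the unconditional contrast is planned and would tend to reveal a training component that did nothing. A reader might also infer that comparing Training Only with a Baseline averaged over all therapists is invalid. It is not: "We will randomize volunteer therapists within each site to study condition at the start of the Implementation phase", so Baseline precedes allocation, and the all-therapist mean is a legitimate and more precise comparator.

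Two points remain. The exploratory label does not change what the pooled contrast estimates. And the two sections still give different instructions when the interaction is not significant.

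**Conclusion.** Wrong as written, with modest severity. The pooled Aim 1 contrast estimates the Training Only change plus p × b. Under 1:1 allocation it exceeds the Training Only change by .15 SD at the plan's planning effect, and by .20 to .25 SD at the values cited from previous research. Those values are illustrations: the protocol states no expected add-on effect of its own beyond the d = .30 used for power, and no allocation ratio in the text shown. The algebra itself needs no assumption beyond some therapists receiving the full package.

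The design and analysis sections are inconsistent on whether the Training Only contrast depends on the interaction, and on its Baseline comparator. The interaction is a weak filter: power of about .31 to .33 at an add-on of .40 with 288 tapes split 1:3, and 5% if the add-on is zero, which is when training alone would account for the whole change. These figures show that the rule matters where it is followed; they are not the chance that the result is lost, since Trial design promises it regardless. Severity is limited because Aim 1 is exploratory and Aim 2 is unaffected.

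**What to change.** In Trial design, describe the Aim 1 pooled Phase contrast as the average change over the two conditions as allocated, and drop its description as the effect of the training component.

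In the Data analysis plan, list the Training Only and the full-package Phase contrasts, each with a confidence interval, to be reported whatever the interaction shows. Remove the rule that makes them depend on a significant interaction; the interaction estimate itself can stay, with its interval.

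State one Baseline comparator and use it in both sections. All-therapist Baseline or own-condition Baseline is a modelling choice; either is acceptable if named in advance.

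Keep the words quasi-experimental and exploratory for these contrasts. They remain uncontrolled before-and-after changes, so any drift over the study period is still mixed into them.

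The cost is a few sentences and no new data. The Training Only interval will be wider than the pooled one: by a factor of .192/.136 = 1.41 against own Baseline, or .152/.136 = 1.12 against all-therapist Baseline, under the assumptions in the working.
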